# Effects of vitamin D and/or magnesium supplementation on mood, serum levels of BDNF, inflammatory biomarkers, and SIRT1 in obese women: a study protocol for a double-blind, randomized, placebo-controlled trial

**DOI:** 10.1186/s13063-020-4122-9

**Published:** 2020-02-26

**Keywords:** Vitamin D, Magnesium, Mood, Brain-derived neurotrophic factor, Inflammatory biomarkers, Sirtuin 1, Obese women

## Abstract

**Background:**

Emerging evidence has shown that vitamin D and magnesium have anti-inflammatory and anti-depressant effects. Dietary intake of magnesium is associated with reduced body mass index, waist circumference, body fat percentage, as well as inflammatory biomarkers and depressive symptoms. Vitamin D deficiency has been linked to inflammation, obesity, and depressive symptoms. This study will test the effects of vitamin D and magnesium co-supplementation on mood, serum level of brain-derived neurotrophic factor (BDNF), inflammation, and sirtuin 1 (SIRT1) in obese women.

**Methods:**

We will conduct an 8-week, double-blind, randomized, placebo-controlled clinical trial, in a factorial design, to evaluate the individual effects of vitamin D and magnesium, and co-supplementation of them, on mood, serum level of BDNF, inflammation, and SIRT1 in 108 obese women.

**Discussion:**

We hypothesize that vitamin D and magnesium co-supplementation may provide a new adjuvant therapy through modulation of BDNF, inflammation, and SIRT1 in obese women.

**Trial registration:**

Iranian Registry of Clinical Trials, IRCT20090822002365N23. Registered on 16 August 2019.

## Background

Depression is a global problem with widespread public health concern [1]. It affects 300 million people globally with a lifetime prevalence of 17% and has been projected to be the largest contributor to disease burden by the year 2030 (https://www.who.int/mental_health/management/depression/wfmh_paper_depression_wmhd_2012.pdf). Depression is linked with high morbidity and mortality, and can have a large negative socioeconomic impact due to associated functional disabilities and knock-on healthcare expenditures [2, 3]. Treatment options consist of antidepressant medications and/or psychotherapy, which are effective in relieving some of the effects of depression. However, over half of all people on these medications experience side effects, which can result in discontinuation of treatment [4]. Therefore, there is an urgent need for new treatment approaches with high efficacy and low side-effect profiles.

In a similar manner, obesity is also a global public health problem. In 2016, approximately 1.9 billion adults were classified as overweight (body mass index (BMI) > 25 kg/m^2^), with one-third of these being obese (BMI > 30 kg/m^2^) (https://www.who.int/news-room/fact-sheets/detail/obesity-and-overweight). As with depression, obesity is associated with decreased quality of life and reduced life expectancy [5]. This is due to the fact that obesity is also a major risk factor for non-communicable diseases such as heart disease, stroke, diabetes, and some cancers [6]. Recent evidence has emerged that there is a bidirectional relationship between obesity and depression as the occurrence of one of these disorders increases the risk of developing the other [7]. Thus, further studies are needed to increase our understanding of the underlying mechanisms associated with both conditions, which may lead to improved treatment options.

Obesity has been found to increase the risk of comorbid depression by 55%, and depression leads to a 58% increased risk of developing obesity [8]. Also, a number of epidemiological and meta-studies have demonstrated that obesity and depression are frequent co-occurring medical conditions [9–14]. Investigations on the mechanisms linking these two disorders have come to the consensus of dysfunctions in neuroendocrine, inflammation, and oxidative stress networks [15, 16]. A number of studies have now shown that depression is marked by chronic inflammation and that treatment with anti-cytokine therapies ameliorated the depressive symptoms [8, 17]. Likewise, the metabolic disruptions in obesity can result in systemic inflammation and treatments with anti-inflammatory agents are considered a novel therapeutic approach to ameliorate the obesity-related insulin resistance and other metabolic disturbances [18].

A number of other studies have also demonstrated that vitamin and mineral deficiency may play a role in both of these disorders. Magnesium is a vital element in higher organisms which regulates biochemical processes in multiple organ systems, including the brain [19]. A preclinical study showed that mice with low magnesium levels had increased belligerent behavior, with elevated levels of noradrenalin compared to control mice with normal magnesium levels [20]. Clinical studies found an inverse relationship between circulating magnesium concentrations and depressive symptoms [21–24]. Furthermore, one study showed that consumption of 500 mg magnesium oxide tablets for 8 weeks by depressed patients with magnesium deficiency led to improvements in depressive symptoms and magnesium levels [25]. Other studies have found antidepressant-like activities of magnesium supplementation in bipolar disorder [26], in women with premenstrual syndrome [27], in individuals with chronic fatigue syndrome [28], and in elderly individuals with depression, hypomagnesemia, and type 2 diabetes [29].

Magnesium deficiency can result in changes in cellular function, leading to the onset of metabolic disorders associated with inflammation, particularly in obese individuals with hypomagnesemia [30–32]. Some studies reported that dietary intake of magnesium is inversely related to physiometric measures such as BMI, waist circumference, and body fat composition [33, 34]. Hypomagnesemia also leads to decreased antioxidant enzyme activities, with concomitant increased production of damaging reactive oxygen species (ROS) by inflammatory cells [35].

Several studies have shown that vitamin D is essential for normal brain development and function, and vitamin D deficiency has been linked with neurological disorders, including depression [36–38]. Vitamin D is also involved in the initial biosynthetic stages of serotonin, a neurotransmitter which has been implicated in both depression and the mechanism of action of antidepressant drugs [39]. Vitamin D deficiencies have also been linked to obesity [38]. For example, studies have found inverse relationships of vitamin D with total body fat and metabolic syndrome [40]. A study also found decreased hippocampal levels of brain-derived neurotrophic factor (BDNF) in a preclinical model of depression, and these were normalized by vitamin D administration [38].

The well-known link of BDNF with depression has led to its frequent use as a potential biomarker in psychiatric disorders [41, 42]. However, its link with obesity is not well understood. In a rodent study, BDNF was found to regulate appetite via modulation of melanocortin signaling [38]. Furthermore, vitamin D deficiency has been associated with serum concentrations of inflammatory biomarkers including interleukin (IL)-6, tumor necrosis factor (TNF)-α, and C-reactive protein (CRP) in obese individuals [43], and increased dietary intake of vitamin D has been linked with lower visceral adiposity and adipocyte size [43].

Other metabolic processes have also been linked with both obesity and depression. The sirtuins are NAD^+^-dependent protein deacetylases in most cells with known roles in metabolism, the stress response, and aging [44]. Levels of SIRT1 have been found to be low in obesity and aging, and normalization of SIRT1 levels decreases disease effects [44]. Studies have also found that SIRT1 promotes insulin signaling through an anti-inflammatory mechanism and suppresses proinflammatory gene expression in adipocytes [45]. Also, the reverse association between SIRT1 and adipose tissue mass and inflammation was found to be normalized by vitamin D [43].

On the other hand, multiple steps in vitamin D metabolism and function require magnesium as a cofactor, including vitamin D binding to vitamin D binding protein, 25(OH)D synthesis, 1,25(OH)_2_D synthesis, 25-hydroxylase synthesis, and vitamin D receptor expression. In addition, serum 1,25(OH)_2_D levels remain low in individuals with magnesium deficiency even following vitamin D intake [46]. Magnesium deficiency has also been found to reduce parathyroid hormone production and the number of vitamin D receptors in target cells [46].

There is not enough information about the individual effect of vitamin D and magnesium on mood, BDNF, and SIRT1 and about co-supplementation. The aim of this study is to evaluate the effects of vitamin D and magnesium co-supplementation on behavioral measures of mood, circulating BDNF and inflammation-related biomarkers, and levels of SIRT1 in obese women.

## Methods

### Design

We will conduct an 8-week, double-blind, randomized controlled trial in a factorial design. Participants will be recruited from staff at the Iran University of Medical Sciences through advertisements. The trial will be conducted over 8 weeks to evaluate the effects of vitamin D_3_ (50,000 IU, one dose weekly) and magnesium (250 mg magnesium oxide, one dose daily) in obese women. The output measures will be behavioral readouts of mood, circulating levels of BDNF, cytokines, and SIRT1 (Figs. 1 and 2). The protocol is written in line with the Standard Protocol Items: Recommendations for Interventional Trials (SPIRIT) checklist (Additional file 1).

**Fig. 1 Fig1:**
[figure not shown]
Protocol flow diagram; we will carry out an 8-week, double-blind, randomized controlled trial to determine the effects of vitamin D and/or magnesium supplementation on mood, serum level of brain-derived neurotrophic factor (BDNF), inflammation, and sirtuin 1 (SIRT1) in obese women. BMI body mass index

**Fig. 2 Fig2:**
[figure not shown]
Timeline of the study; we expect 18 months for this trial

### Objectives and hypotheses of the study

The primary objective of the present study is to assess the effects of vitamin D_3_ and magnesium co-supplementation in obese women on readouts of mood, serum levels of 25(OH)-D, magnesium, BDNF, inflammatory biomarkers (hs-CRP, TNF-α, IL-6), and sirtuin 1 levels. For controlling of confounder factors, the study will evaluate anthropometric indices (weight, body mass index, and waist circumference), dietary intake of energy and macronutrients, and physical activity levels in the women at baseline and at the end of the study.

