### Sample size

To estimate the sample size, we considered α = 0.05 and β = 0.20 in line with previous trials. In addition, we used 1570.5 ng/ml as the standard deviation and 1250.0 ng/ml as the mean of hs-CRP levels as the primary variable, as described previously [47]. This resulted in a requirement of 25 participants in each group. To allow for attrition, 27 participants will be recruited for each group, giving a total of 108 obese women.

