### Statistical analysis

Statistical tests of the outcome measures will be performed using SPSS (version 22.0; SPSS Inc., Chicago, IL, USA). The normality of distribution will be examined and confirmed by the Kolmogorov–Smirnov test. All results will be expressed as mean ± SD. Categorical variables will be presented as frequencies and percentages. The chi-square test will be used to test for differences between categorical variables. Baseline mean differences will be tested using one-way analysis of variance (ANOVA). Analysis of covariance (ANCOVA) will be used to identify differences between the four treatment arms at the end of study, adjusting for baseline values and covariates. The comparison of mean values will be done within groups after the intervention period using paired-sample *t* tests. Bonferroni corrections will be used in pairwise comparisons of the values after the intervention. *P* < 0.05 will be considered statistically significant.

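### The sample size rests on hs-CRP as the primary variable, but the primary objective lists eight unranked outcomes with no stated correction across them, so it is unclear which result decides the trial

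*Protocol article*

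**What the plan says.** Three parts of the Methods in the protocol article bear on this.

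- **Objectives and hypotheses of the study.** The section states one primary objective, which is to look at co-supplementation and its effects "on readouts of mood, serum levels of 25(OH)-D, magnesium, BDNF, inflammatory biomarkers (hs-CRP, TNF-α, IL-6), and sirtuin 1 levels". Counted out, the list is mood, 25(OH)D, magnesium, BDNF, hs-CRP, TNF-α, IL-6 and SIRT1. None is ranked above another, and hs-CRP appears only inside a bracket as one of three inflammatory markers.
- **Sample size.** "we considered α = 0.05 and β = 0.20 in line with previous trials", with "1570.5 ng/ml as the standard deviation and 1250.0 ng/ml as the mean of hs-CRP levels as the primary variable". "This resulted in a requirement of 25 participants in each group", and with an allowance for attrition "27 participants will be recruited for each group, giving a total of 108 obese women".
- **Statistical analysis.** ANCOVA compares the four arms at the end of study. Bonferroni is stated for pairwise comparisons of post-intervention values. P "< 0.05 will be considered statistically significant", with no division of that level across outcomes.

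Outcome measures describes how each variable is measured and marks none as primary. The title and abstract name mood, BDNF, inflammation and SIRT1 together.

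**The concern.** A trial sized for one outcome at α = 0.05 controls its error for that outcome only. If the primary objective spans eight outcomes, each judged at 0.05, neither the error rate nor the power in the sample size describes the objective as written. Bonferroni between arms does not help, because it limits error within one outcome and not across outcomes.

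Two of the eight also differ in kind from the rest. Participants are enrolled with low serum 25(OH)D and magnesium and are then given those nutrients, so a rise in the corresponding blood level shows exposure rather than benefit. Placing these two under the primary objective on the same footing as mood or hs-CRP blurs what the trial sets out to show.

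At stake is whether a reader of the results can tell, from a plan fixed in advance, which comparison was the confirmatory one.

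**Working it through.** **Inputs.** SD 1570.5 ng/ml, the 1250.0 ng/ml figure, α = 0.05, β = 0.20, and 25 and 27 per group come from Sample size. The eight outcomes come from Objectives. The 0.05 threshold and the four-arm comparison come from Statistical analysis. The article gives no correlation between outcomes, so a range from 0 to 0.8 is assumed.

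**Step 1: reproduce the plan's figure.** For two means, two-sided, normal approximation:

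n = 2 (z₀.₉₇₅ + z₀.₈₀)² (SD/Δ)² = 2 × (1.960 + 0.842)² × (1570.5/1250)² = 24.8, so 25 per group.

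This matches the article when 1250.0 ng/ml is read as the difference to be detected (the article calls it a mean). Power with 25 per group is 80.3%. The sample size is therefore that of a single outcome tested at the full 0.05.

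**Step 2: error across outcomes, if any one significant result were taken as enough.** With k independent outcomes and no true effect on any, the chance of at least one false positive is 1 − 0.95^k.

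- k = 1: 5%
- k = 6 (mood, BDNF, hs-CRP, TNF-α, IL-6, SIRT1): 1 − 0.95⁶ = 0.265
- k = 8 (all listed): 1 − 0.95⁸ = 0.337

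Correlation lowers these figures. Four-arm F tests were simulated with 25 per arm, equal correlation between outcomes, no true effects and no covariate adjustment:

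| Assumed correlation | Six outcomes | All eight |
|---|---|---|
| 0 | 26% | 34% |
| 0.3 | 24% | 31% |
| 0.5 | 21% | 26% |
| 0.8 | 15% | 16% |

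The six-outcome column is the more relevant one. Serum 25(OH)D and magnesium are expected to rise truly in the supplemented arms, so they should not be counted as null.

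**Step 3: what keeping all eight as primary would imply.** Bonferroni gives 0.05/8 = 0.00625, with z = 2.734.

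- Required size for hs-CRP: 2 × (2.734 + 0.842)² × (1570.5/1250)² = 40.4, so 41 per group before attrition.
- Power for hs-CRP at the planned size: 53% with 25 per group, 58% with 27.

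For the six outcomes alone, 0.05/6 = 0.00833 requires 39 per group and gives 57% power with 25. The planned 108 women therefore support one primary outcome, not six or eight, on the article's own assumptions.

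**The case against.** **A primary variable is named.** Sample size gives hs-CRP that role explicitly. A reader might infer from the Objectives list that hs-CRP has no special status, but the article does not support that. What stands against the plan is narrower: one section gives hs-CRP the role, another lists it level with seven others, and no section reconciles the two.

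**No success rule is stated.** An objective to assess effects on a list is not a rule that any one significant result meets it. A reader might infer such a rule, or expect a rise in 25(OH)D to be reported as success, but nothing in the article says so. The error figures must therefore be conditional on that reading.

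**One in three is too high as a headline.** The 34% needs eight outcomes that are all independent and all null. Two of them are expected to move, and the three inflammatory markers are probably correlated. This objection is sound, and the six-outcome range is the fairer one.

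**The article condenses a fuller protocol.** A correction across outcomes might be set out in a document not shown, so its absence alone would not be a finding. The conflict between Objectives and Sample size, however, is on the page.

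**The choice of primary outcome belongs to the sponsor.** The title leads with mood and BDNF, and splitting α is a legitimate alternative. That is also fair, but splitting α carries the power cost shown in the working.

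**Conclusion.** The point holds as an inconsistency about which outcome is primary. Objectives and Sample size cannot both serve as the definition, and the stated multiplicity step does not cover the difference.

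The size of the problem is conditional. If significance on any listed outcome were read as meeting the primary objective, the chance of at least one false positive among the six outcomes that are not the supplements' own levels would be about 26% under independence and about 15% at a correlation of 0.8. The corresponding range for all eight is about 34% down to 16%, and its upper end applies only if all are independent and null. These figures assume no true effects and equal correlation, and the correlations are assumed because the article gives none. Every scenario is about three times the nominal 5% or more.

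The sample size itself is sound arithmetic for one outcome at 0.05, with 1250.0 ng/ml read as a difference.

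**What to change.** Before unblinding, amend Objectives and hypotheses of the study as follows:

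1. Name hs-CRP, the outcome used for the sample size, as the single primary outcome at α = 0.05.
2. Make BDI, BDNF, TNF-α, IL-6 and SIRT1 secondary, and state either a correction across those outcomes (Holm would do) or that they are exploratory.
3. Report serum 25(OH)D and magnesium as exposure markers.
4. Use the same hierarchy in Outcome measures and Statistical analysis.

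This changes wording only. It needs no extra participants or visits, and the 25 per group stands. The price is that mood, BDNF and SIRT1, which are prominent in the title, become secondary claims.

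If the sponsor prefers several primary outcomes, α must be split across them, and the power for each must be restated at the planned size or the sample size recalculated.

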### Participants

Participants will be 108 obese women. The inclusion criteria will consist of: BMI = 30–40 kg/m^2^; age = 18–50 years; serum 25(OH)D < 30 ng/ml; serum magnesium ≤ 2 mg/dl; no indication of hormonal changes, autoimmune disease, diabetes, hypertension, or renal, hepatic, parathyroid, hormonal, and gastrointestinal disorders; not pregnant, breast-feeding, or menopaused; not taking vitamin D and/or magnesium supplements and other vitamin–mineral supplements or antidepressant drugs; not taking laxative and/or anti-inflammatory medications; and not having had a weight loss of ≥ 3 kg within 2 months leading up to the trial. Exclusion criteria will be less than 90% compliancy with the treatment.

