### Randomization

Randomization to the different treatment arms will be performed using computer-generated random numbers. The 108 participants who meet the criteria will be allocated as such into four treatment groups: 50,000 IU vitamin D soft gel (weekly), plus a 250-mg magnesium tablet (daily); 50,000 IU vitamin D soft gel (weekly) plus a magnesium placebo (daily); vitamin D placebo (weekly) plus a 250-mg magnesium tablet (daily); and a vitamin D placebo (weekly) plus a magnesium placebo (daily). The vitamin D soft gels and magnesium tablets are provided by Zahravi, Iran and Jalinous, Iran, respectively. The placebos for vitamin D and magnesium contained oral paraffin and maltodextrin, respectively, and are supplied by Zahravi, Iran (these were matched in appearance of the corresponding soft gels and tablets). Patients will receive verbal and written counseling on how to consume the supplements and compliance will be evaluated by tablet count every 2 weeks.

For blinding, a person who is not involved in the study protocol will create a randomized list assigning participants to each treatment arm. The soft gels, tablets, and corresponding placebos will be placed into unlabeled identical containers. The study leader will label the containers with participant numbers using the codes generated through the randomization. All investigators and participants will be blinded.

Women who meet the inclusion criteria will be informed completely about the protocol of the study. The ethics committee will review and approve the final study protocol. Each participant will sign the informed consent form.

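### The 90% compliance exclusion can only act after randomisation and, followed as written, would leave selected subsets of the four arms; its effect on sample size depends on an unstated counting rule

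*Protocol article*

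**What the plan says.** The Participants section lists eligibility conditions under inclusion and then gives a single exclusion criterion: "Exclusion criteria will be less than 90% compliancy with the treatment".

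The Randomization section says that "The 108 participants who meet the criteria will be allocated as such into four treatment groups". Each woman takes one weekly soft gel and one daily tablet, active or matched placebo, and "compliance will be evaluated by tablet count every 2 weeks".

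The Sample size section derives 25 per group and then adds a margin: "To allow for attrition, 27 participants will be recruited for each group, giving a total of 108 obese women". It does not mention losses through the compliance rule.

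The Statistical analysis section compares the four arms at the end of the study by ANCOVA, adjusted for baseline values and covariates. It does not say what happens to a woman who fell below 90%.

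**The concern.** An exclusion criterion normally acts before allocation. This one depends on how much study product a woman takes, which cannot be known until she has been randomised and dispensed it. Following it means removing randomised women because of something that happened afterwards.

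Randomisation makes the arms comparable as whole groups. It does not make the compliers of one arm comparable with the compliers of another. Compliance can depend on tolerability, which may differ between active product and placebo, and on mood, which the trial measures as an outcome. Adjusting for baseline values does not repair selection on unmeasured causes of non-compliance. Every between-arm estimate is exposed, including that for hs-CRP, the variable used to size the trial.

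A second, smaller matter is numbers. The margin above the required 25 is two women per arm, and the protocol does not say how the 90% is counted across a weekly and a daily product. Under one way of counting, the rule alone could use up that margin.

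**Working it through.** **1. When the rule can act.** Eligibility is settled before allocation, and compliance counts start after it, every 2 weeks. No run-in is described. Every woman the rule removes has therefore already been randomised.

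**2. The plan's own sample size.** Inputs from the Sample size section: α = 0.05, β = 0.20, SD 1570.5 ng/ml and 1250.0 ng/ml. The last figure is called a mean, but it reproduces the stated number only when used as the difference between two groups, with a two-sided test:

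n = 2 × [1570.5 × (1.960 + 0.842) / 1250]² = 24.8, so 25 per group.

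The 27 recruited leave 27 − 25 = 2 spare per arm, or 2/27 = 7.4%, and 4 × 27 = 108. The stated figures reproduce.

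**3. What 90% means in doses.** Eight weeks give 8 soft gels and 56 tablets, 64 units in all. The document does not say which count applies.

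| Count | Fewest misses that exclude | Compliance then |
|---|---|---|
| 8 soft gels | 1 | 7/8 = 87.5% |
| 56 tablets | 6 | 50/56 = 89.3% |
| 64 units pooled | 7 | 57/64 = 89.1% |

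**4. Share excluded under each count.** The document gives no adherence figures. As an assumption, let each dose be taken independently with probability q. The share excluded is 1 − q⁸ for soft gels, P(6 or more missed of 56) for tablets and P(7 or more missed of 64) for the pooled count, the last two from the binomial distribution with miss probability 1 − q.

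| q | Soft gels alone | Tablets alone | Pooled |
|---|---|---|---|
| 0.99 | 7.7% | 0.002% | 0.0004% |
| 0.98 | 14.9% | 0.09% | 0.03% |
| 0.97 | 21.6% | 0.7% | 0.3% |

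Against an allowance of 7.4% for all losses, the soft-gel count exceeds it at each of these values, while the other two barely touch it. At q = 0.95 the tablet and pooled figures are 6.0% and 4.0%, still within the allowance if there were no other losses.

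**5. What a given loss does to power.** At q = 0.97 on soft gels, 27 × (1 − 0.216) = 21.2, so about 21 per arm remain. For one pairwise comparison without multiplicity correction, with d = 1250/1570.5 = 0.796, t-based power is 0.819 at 27 per arm, 0.787 at 25 and 0.711 at 21.

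**6. How thin the margin is for losses of any cause.** A third loss takes an arm below 25. With independent losses at an assumed rate p, P(3 or more of 27 lost) is 15% at p = 5% and 52% at p = 10%. The chance that at least one of four arms falls below 25 is 1 − (1 − that value)⁴, which is 48% and 94%.

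**7. Bias.** No calculation is possible. It would need non-compliance by arm and its relation to outcome, and the document gives neither.

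**The case against.** The strongest reply is that the protocol never says non-compliers leave the analysis. The criterion is one sentence under Participants; it could concern treatment, follow-up or the analysis set, and the ANCOVA description is not restricted to compliers. This stands in part. A reader might infer that the trial has committed itself to a per-protocol analysis, and the text does not go that far. A reader might also treat the lack of a stated intention-to-treat analysis as a defect in itself. It is not one here, because a full protocol or SAP not shown may define the analysis sets. What remains is a stated rule to exclude, which nothing in the article offsets. If it also ends follow-up, the week-8 outcomes are never collected and no later analysis plan can recover them.

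A second reply is that the trial is double-blind with matched placebos and every woman takes the same two kinds of product, which makes non-compliance less likely to differ by arm. That is fair and lowers the risk. It does not remove it, because differences in tolerability or in effect on mood can still change behaviour under blinding.

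A third reply is that the loss of power depends on one way of counting. This stands. It would be tempting to conclude that the attrition allowance will be exhausted and power will fall to 71%. That needs the 90% to be applied to the soft gels alone and q = 0.97. Under pooled or tablet-only counting, the same model makes the effect almost vanish. Independence is itself an assumption; clustered non-compliance would give other figures.

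**Conclusion.** The point holds as a defect in a stated rule. The only exclusion criterion operates after randomisation, and following it would replace the randomised comparison with one between self-selected subsets. That conclusion needs no numerical assumption beyond reading the sentence as written. The direction and size of the bias are unknown.

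The sample-size consequence is conditional and should not carry the weight of the point. Over q from 0.97 to 0.99 with independent doses, the rule excludes 7.7% to 21.6% if applied separately to the soft gels, and at most 0.7% on tablets or 0.3% pooled, against an allowance of 7.4% for every kind of loss. The document does not settle which count is meant, and that ambiguity needs resolving in its own right because the three counts would exclude different women.

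**What to change.** State in the protocol that compliance below 90% is not a reason to exclude a randomised woman from follow-up or from the primary analysis. Take the week-8 measurements on all randomised women where possible, whatever their compliance. Run the primary ANCOVA by arm as randomised. Keep at least 90% compliance only to define a supportive per-protocol analysis, and say how it is counted: each product separately, tablets only, or both pooled.

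This concerns follow-up and analysis only. If the sentence was also meant as a rule about continuing treatment, the sponsor should say so separately; no change to such a rule is proposed here.

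The cost is a change of wording and a few extra week-8 visits. The statistical downside is some dilution of the estimated effect by women who took less than the full course. In return, compliance exclusions take nothing from the two spare women per arm.
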